#### Withdrawal

Patients can leave the study at any time for any reason if they wish to do so without any consequences. The coordinating investigator can decide to withdraw a patient from the study for urgent medical reasons. After withdrawal, individual patients will not be replaced. If a patient is withdrawn from the study, follow-up ends.

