### Sample size calculation and drop-out

A sample size calculation is performed for the primary outcome of anatomical success at 12 months.

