### Data analysis plan

The intention-to-treat (ITT) population will include all patients randomised to one of the two treatment groups. These groups will be analysed according to the ITT principle (analysed as randomised). The per-protocol (PP) population will only include those patients who underwent the procedure they were randomised to. Statistical analysis will be performed by using SPSS (IBM SPSS Statistics V.25).

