#### Primary outcome analysis

Anatomical success at 12 months of follow-up is a dichotomous variable and will be described as numbers with percentages. The difference between the two groups will be presented as a percentage with a 95% CI. If the lower limit of this CI does not exceed the non-inferiority margin of −10%, the intervention will be considered to be non-inferior. A second analysis will be performed in which data from the last follow-up visit before a reintervention will be used in patients undergoing a reintervention of the GSV after failure of primary treatment.

These analyses will be performed for both the ITT and the PP population. Patients with missing data on the primary outcome parameters will be excluded from analyses.

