### Adverse events and reportable events

All adverse events (AEs) reported spontaneously by the subject or observed by the research coordinator or other members of the study team will be recorded. The following events are considered reportable events:

Any serious AE that has a causal relationship with the investigational device, the comparator or the investigation procedure or where such causal relationship is reasonably possible.Any device deficiency that might have led to a serious AE if appropriate action had not been taken, intervention had not occurred or circumstances had been less fortunate.Any new findings in relation to any event referred to in points (a) and (b).

The research coordinator will report all reportable events to the sponsor without undue delay but not later than 3 calendar days after obtaining knowledge of the event. Reportable events that are (possibly) related to the investigational procedure will be reported to the accredited Medical Ethical Review Committee (METc) that approved the protocol through the web portal ToetsingOnline using the form MDCG 2020-10/2. Reportable events that are not related to the investigational procedure will be reported to the manufacturer.

All AEs will be followed until they have abated, or until a stable situation has been reached. Depending on the event, follow-up may require additional tests or medical procedures as indicated, and/or referral to the general physician or a medical specialist. Serious AEs need to be reported till the end of the study within the Netherlands, as defined in the protocol.

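### Withdrawal by the investigator ends all follow-up, which loses outcome and safety data that could be kept with consent and conflicts in wording with the adverse-event rule

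*Protocol article*

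**What the plan says.** The Withdrawal section of the protocol article allows patients to leave at any time. It adds a second route: "The coordinating investigator can decide to withdraw a patient from the study for urgent medical reasons". Both routes have the same consequence, without exception: "If a patient is withdrawn from the study, follow-up ends". It also says: "After withdrawal, individual patients will not be replaced".

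The Data analysis plan defines the main population broadly: "The intention-to-treat (ITT) population will include all patients randomised to one of the two treatment groups". The Primary outcome analysis section, which covers both the ITT and the per-protocol analyses, then adds: "Patients with missing data on the primary outcome parameters will be excluded from analyses".

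The section on adverse events and reportable events is equally unqualified: "All AEs will be followed until they have abated, or until a stable situation has been reached". It continues: "Serious AEs need to be reported till the end of the study within the Netherlands, as defined in the protocol".

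According to Randomisation and blinding, the coordinating investigator carries out the randomisation, and allocation cannot be concealed from patients or surgeons.

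**The concern.** Each arm receives one procedure. Once it is done, an investigator's decision to withdraw a patient stops no study treatment; it only stops data collection. The rule makes no distinction between a patient who refuses further contact and a patient whom the investigator withdraws but who would still attend.

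Three things could follow. First, the 12-month duplex result of such a patient is lost, and the complete-case rule removes the patient from an ITT analysis defined as all randomised. Second, the decision is taken by someone who knows the arm. If the medical reason is related to the treatment or its result, the missing data are informative, and in a non-inferiority trial the loss of failures from the new-treatment arm favours the conclusion sought. Third, a patient withdrawn for a medical reason may well have an open adverse event. One section ends that patient's follow-up and another requires it to continue.

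**Working it through.** **1. The route from withdrawal to analysis.** Withdrawal before 12 months means no follow-up, hence no 12-month duplex, hence a missing primary outcome, hence exclusion from both the ITT and the per-protocol primary analysis. Each link is written in the protocol.

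**2. The plan's own sample size.** Inputs from the Anatomical success part of the sample size section: EVLA 95%, Flebogrif 93%, margin 10 points, one-sided 2.5%, power 80%, 10% loss.

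n per arm = (1.960 + 0.842)² × (0.95×0.05 + 0.93×0.07) / (0.10 − 0.02)² = 138.1, rounded up to 139, so 278 in total. Inflated: 139 / 0.9 = 154.4, rounded up to 155, so 310 in total. Both figures reproduce. The 10% allowance protects precision; it does not protect against bias from who is lost.

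**3. Expected distance to the margin.** With 139 evaluable patients per arm at the design rates, the standard error is √[(0.93×0.07 + 0.95×0.05)/139] = 2.85 points. The lower Wald limit is −2.0 − 1.96×2.85 = −7.6, which is 2.4 points from −10.

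**4. Sensitivity to a few recovered failures (illustration).** Take whole patients close to the design rates, Flebogrif 129/139 and EVLA 132/139, and add back withdrawn Flebogrif patients who all failed:

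| Flebogrif | EVLA | Difference (points) | Lower 95% limit |
|---|---|---|---|
| 129/139 | 132/139 | −2.2 | −7.8 |
| 129/140 | 132/139 | −2.8 | −8.6 |
| 129/141 | 132/139 | −3.5 | −9.3 |
| 129/142 | 132/139 | −4.1 | −10.1 |
| 129/142 | 132/140 | −3.4 | −9.5 |

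Each failure costs about 0.8 points. Three failures, all in the Flebogrif arm, cross the margin; one offsetting EVLA failure (last row) brings the limit back inside it.

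A second series adds back the full allowance of 16 Flebogrif patients (155 − 139), with EVLA at 147/155. For 0 to 5 failures among the 16 the limits are −6.5, −7.3, −8.0, −8.8, −9.6 and −10.3. The slope is again about 0.8 points, but five of the 16 must fail before the margin is crossed. The two series start from different limits and must not be mixed.

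**5. Error rate under assumed missingness.** None of these inputs comes from the protocol. Set the true rates at the margin (85% against 95%), with 10% of EVLA patients missing at random and 2% of Flebogrif patients missing. The one-sided error is 2.5% if the missing Flebogrif patients fail at their arm's own rate of 15%, 4.0% if half fail and 7.5% if all fail. With 5% of Flebogrif patients missing, the figures are 2.5%, 8.0% and 29.8%.

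**6. The two rules side by side.** The Withdrawal section ends follow-up for every withdrawn patient. The adverse-event section requires follow-up of every adverse event until it has abated or is stable, and reporting of serious events to the end of the study. Neither makes an exception for the other. For a withdrawn patient with an open event, both cannot be followed as worded.

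**The case against.** The strongest reply is that nothing in the protocol ties an urgent medical withdrawal to anatomical failure. Complications are outcomes recorded through 60 months, not stated triggers for withdrawal. Failure of the vein leads to a recorded reintervention, with its own second analysis, and recanalisation on duplex is hardly an urgent medical reason. This stands. A reader might infer that the clause biases the primary comparison; the text supports a risk only.

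A reader might also infer that DVT, pulmonary embolism and nerve injury go unrecorded. That goes too far, because an event that prompts withdrawal has already occurred and been noted. What can be lost is its course and any later event.

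Randomisation precedes treatment, so some withdrawals may occur before the procedure. Those patients have no treated segment to scan. This also stands and limits the point to treated patients.

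The word follow-up may mean only the scheduled visits, with adverse-event care running separately. That reading is possible, but the Withdrawal section does not say so, and removing the ambiguity is part of the remedy.

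Finally, the damage to the analysis comes through the complete-case rule, which applies to all missing data. That is true, but no analysis can recover observations that the protocol says to stop collecting.

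**Conclusion.** The point holds in a limited form and merits an amendment. As written, the plan stops outcome and safety data collection for treated patients whom an unblinded investigator withdraws, even when they would agree to continue, and then removes them from both primary analyses if the 12-month result is missing. The loss is avoidable only for such patients and for those who leave but would accept limited data collection; it is unavoidable when consent for data collection is withdrawn.

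The size is unknown because the expected number of withdrawals is not given, and it is small if they are few. The slope of about 0.8 points per Flebogrif failure, against 2.4 points of expected room, shows sensitivity and does not estimate bias. It assumes Wald limits, results near the design rates, and lost patients who are all failures in one arm. A reader might conclude that three withdrawals would overturn the result; that needs exactly this one-sided pattern, and one EVLA failure undoes it.

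The conflict with the adverse-event section is one of wording. It needs no assumption about bias.

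**What to change.** Amend the Withdrawal section as follows:

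- Only a patient's withdrawal of consent for data collection ends outcome follow-up.
- Treated patients withdrawn by the investigator stay in the ITT population and, if they agree, continue the scheduled outcome and safety data collection, including the 12-month duplex.
- Patients who choose to leave are asked whether a 12-month duplex, or data from their records, may still be collected.
- The Withdrawal and adverse-event sections are reconciled on what happens to open adverse events after withdrawal. Which rule should apply is for the sponsor and the ethics committee to settle.

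The cost is a protocol amendment and revised consent wording. Enrolment began in September 2021 and was expected to finish around October 2024, so the wording must also reach participants already enrolled. No visits are added beyond those planned and the sample size stays at 310. On the design assumptions, power is 80.3% with 139 evaluable patients per arm and would be 84.3% if all 155 were retained. The study runs until five years after the last inclusion, so the change would still protect later data.

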### Study treatment

#### Intervention (Flebogrif) group

The included patients randomised to the intervention group will receive treatment with Flebogrif. The Flebogrif device is used to induce a combination of mechanical and chemical damage to the vein wall. The Flebogrif device is equipped with five retractable cutting/scratching elements that cause mechanical damage. The simultaneous, controlled administration of a foam sclerosant, results in chemical damage and obliteration of superficial venous trunks. No tumescent anaesthesia, sedation or antibiotics are required. The surgeons are experienced in the performance of endovascular procedures within the superficial venous system, with particular consideration of the specific nature and methodology of mechanochemical procedures. Prior to treatment, the GSV is marked using ultrasound. The patient is placed in supine position. Standard agents for disinfecting the operating field are used for skin desinfection. Thereafter, the leg is covered with sterile surgical drapes. Venipuncture is performed under ultrasound guidance with a 18G needle. A 0.035” guidewire is introduced through the 18G needle and placed at the level of the connection with the femoral vein (SFJ). The vascular sheath is introduced over the guidewire. After flushing the kit elements, the Flebogrif catheter, with a length of 60 cm, is inserted over the guidewire. The the working part of the tip is positioned at the predefined point, that is, 1 cm below the SFJ. Before releasing the cutting elements of the Flebogrif, the position of the catheter is checked. The cutting elements of the Flebogrif are fixated by clamping the clamping nut (2–3 cm per seconds). If the vein has a diameter of 8 mm or larger, two cutting passages will be performed over the entire length. The core part of the procedure consists of a steady withdrawal of the Flebogrif at a fixed speed, with concomitant injection of the sclerosant foam (3% polidocanol (EasyFoam), 2 mg/kg, 1 on 4 air). During foam injection, the groin is continuously compressed using the ultrasound head. The maximum amount of foam used will be 10 mL (50 cm). After the catheter is removed, manual pressure is applied to the area of the venipuncture. A detailed description of the Flebogrif design, enabling the correct use of the catheter as intended by the manufacturer, is contained in the operating instructions. After treatment, the deep venous system is checked using duplex ultrasound (DUS). If deemed necessary, additional phlebectomy of side branches is performed during the same session. A whole leg compression stocking (20–30 mm Hg) is applied continuously for the first 24 hours and continiued during the day for 1 week. Patients may resume normal activities immediately after the procedure but are given the advice to avoid peak pressure during the first week. If deemed necessary, additional sclerotherapy of side branches is performed during one of the follow-up visits. If additional sclerotherapy is performed, leg compression will be continued for 1 week.

#### Control (EVLA) group

The included patients randomised to the control group will receive treatment with EVLA. Prior to treatment, the GSV is marked using ultrasound. The patient is placed in supine position. Standard agents for disinfecting the operating field are used for skin desinfection. Thereafter, the leg is covered with sterile surgical drapes. Venipuncture is performed under ultrasound guidance with a 18G needle. A 6 F 11 cm sheet is introduced and followed by the introduction and positioning of the tip of the 1470 nm 2ring radial fibre (ELVeS Radial; Biolitec, Austria) 0.5 cm below the SFJ. Perivenous tumescent anaesthesia is administered using lidocaine 0.05% cold saline (5°C–10°C) and a roller pump (Nouvag Dispenser DP20). After administration of the tumescent fluid, the location of the tip of the laser fibre is checked. Laser treatment is performed using a continuous mode with a power of 10–12 watts. By slowly withdrawing the fibre, a targeted energy dose is delivered that is determined by the diameter of the GSV (approximately 80 J/cm). This process is repeated until the entire incompetent vein is ablated. After treatment, the deep venous system is checked using DUS. If deemed necessary, additional phlebectomy of side branches is performed during the same session. A whole leg compression stocking (20–30 mm Hg) is applied continuously for the first 24 hours and continued during the day for 1 week. Patients may resume normal activities immediately after the procedure but are given the advice to avoid peak pressure during the first week. If deemed necessary, additional sclerotherapy of side branches is performed during one of the follow-up visits. If additional sclerotherapy is performed, leg compression will be continued for 1 week.

### Primary outcome

#### Anatomical success (at 12 months)

Anatomical success (at 12 months) is objectified at 12 months follow-up using DUS. DUS is performed with the patient in the upright position, applying manual compression to the calf and using the Valsalva manoeuvre to detect flow and reflux. Occlusion is defined as a non-compressible vein (segment) that subsequently lacks flow and reflux. Recanalisation is defined as a compressible vein (segment) with flow or reflux.

Anatomical success outcomes (at 12 months) are defined as:

Anatomical success: complete occlusion of the treated vein segment or a recanalised segment of ≤5 cm.Anatomical failure:Partial recanalisation: a recanalised segment of >5 cm.Complete recanalisation: recanalisation of the entire treated vein segment.

### Secondary outcomes

#### Intraprocedural pain

Intraprocedural pain is assessed during treatment using an 11-point Numeric Rating Scale (NRS) ranging from 0 (no pain) to 10 (worst pain imaginable).

#### Operation time

Time interval (minutes) between the venipuncture and removal of the catheter.

#### Technical success

The ability to position the device adequately, treat the vein as planned and occlude the treated vein directly after the procedure as proven by DUS.

#### Postprocedural pain

Postprocedural pain is assessed daily during the first week after treatment using an 11-point NRS ranging from 0 (no pain) to 10 (worst pain imaginable).

#### Safety

Occurrence of DVT, pulmonary embolism (PE) or nerve injury within 1 month after treatment.

#### Anatomical success (during other follow-up moments)

Anatomical success (during other follow-up moments) is objectified at 1 week, 1, 6, 24 and 60 month(s) follow-up using DUS. DUS is performed with the patient in the upright position, applying manual compression to the calf and using the Valsalva manoeuvre to detect flow and reflux. Occlusion is defined as a non-compressible vein (segment) that subsequently lacks flow and reflux. Recanalisation is defined as a compressible vein (segment) with flow or reflux.

Anatomical success outcomes (during other follow-up moments) are defined as:

Anatomical success: complete occlusion of the treated vein segment or a recanalised segment of ≤5 cmAnatomical failure:Partial recanalisation: a recanalised segment of >5 cm.Complete recanalisation: recanalisation of the entire treated vein segment.

#### Complications

The occurrence of (thrombo)phlebitis, infection of the puncture wound, haematoma, hyperpigmentation, skin burn, DVT, PE, nerve injury, allergic reaction to polidocanol or migraine is assessed perioperatively and at 1 week, 1, 6, 12, 24 and 60 month(s) follow-up.

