### Exclusion criteria

Bilateral endovenous thermal/MOCA treatment of the GSV.Simultaneous ipsilateral endovenous thermal/MOCA treatment of additional veins.C6 varicose veins.Previous ipsilateral GSV or anterior accessory saphenous vein (AASV) treatment.Superficial thrombophlebitis or deep venous thrombosis (DVT) in the last 6 months.Occlusion of deep venous system.Coagulation disorders or increased risk of thromboembolism.Use of direct oral anticoagulants or vitamin K antagonists.Pregnancy or lactation.Immobilisation.Cognitive impairment or language barrier.Allergy or contraindication to polidocanol.Severe renal or liver insufficiency.

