### Other measurements

Before treatment: gender (female or male); age; medical history (occurrence of migraine, asthma or chronic obstructive pulmonary disease, treatment of other leg vein(s)); use of platelet aggregate inhibitors; treatment side (right or left); baseline general pain score (assessed using an 11-point NRS ranging from 0 (no pain) to 10 (worst pain imaginable)); the presence of an (in)sufficient AASV and its confluence anatomy; GSV diameter (SFJ and mid-thigh) and length.During treatment: treated vein length; power in watts and total joules (EVLA); the amount of polidocanol foam used (Flebogrif); performance of concomitant phlebectomy of side branches.1 week, 1, 6, 12, 24 and 60 month(s) follow-up: treatment of side branches (phlebectomy and/or sclerotherapy (foam vs liquid, amount and percentage of polidocanol used)).

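### The allergy item in the complication list counts reactions to polidocanol only, so a reaction to the tumescent lidocaine used for EVLA cannot count under it

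*Protocol article*

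**What the plan says.** All references are to the protocol article.

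- **Complications** (secondary outcomes) gives ten items. The allergy item reads "allergic reaction to polidocanol or migraine is assessed perioperatively", and assessment continues at all six follow-up visits. It is the only item that names a causal agent. Others, such as "haematoma, hyperpigmentation, skin burn, DVT, PE, nerve injury", are worded as harms whatever their cause.
- **Intervention (Flebogrif) group**: the catheter is withdrawn "with concomitant injection of the sclerosant foam (3% polidocanol (EasyFoam", so polidocanol is part of the index procedure. The same section says "No tumescent anaesthesia, sedation or antibiotics are required".
- **Control (EVLA) group**: "Perivenous tumescent anaesthesia is administered using lidocaine 0.05% cold saline". Polidocanol is not part of the index procedure, but "If deemed necessary, additional sclerotherapy of side branches is performed during one of the follow-up visits".
- **Other measurements** shows that polidocanol is the agent for that later treatment. It records "sclerotherapy (foam vs liquid, amount and percentage of polidocanol used" at the follow-up visits.
- **Exclusion criteria** lists "Allergy or contraindication to polidocanol", for both arms. It has no counterpart for lidocaine.
- **Secondary outcome analysis** names complications among the categorical variables compared by the chi-square or Fisher's exact test.
- **Adverse events and reportable events** records all adverse events that patients report spontaneously or that study staff observe, whatever the agent.

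**The concern.** Each index procedure uses its own drug, and each drug can cause an allergic reaction. The outcome definition names one of the two. The same kind of harm is thus a listed complication, looked for at every visit and tested between arms, when polidocanol causes it. When tumescent lidocaine causes it, it is an adverse event that depends on spontaneous report or observation.

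At stake is one row of the complications table. A reader will take that row as a comparison of allergic reactions under the two techniques, but it compares reactions to one technique's drug. On this row the wording works against Flebogrif. The gap comes from a definition that the article fixes, so it is not a detail left to a fuller document.

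**Working it through.** **The plan's own figure.** The article gives no figure for complications, so the sample size only supplies the arm size. With success of 95% and 93%, a margin of 10 points, one-sided alpha 2.5% and power 80%:

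n per arm = (1.960 + 0.842)² × (0.95 × 0.05 + 0.93 × 0.07) / (0.10 − 0.02)² = 7.85 × 0.1126 / 0.0064 ≈ 138.1, rounded up to 139, or 278 in total.

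Allowing for 10% loss: 139 / 0.9 = 154.4, rounded up to 155 per arm, or 310 in total. Both match the article.

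**What the wording leaves out.** Let p be the chance of a polidocanol reaction in an exposed patient, l the chance of a reaction to tumescent lidocaine, and s the share of EVLA patients who later receive polidocanol sclerotherapy. Ignore the rare patient who reacts to both drugs. Also ignore later sclerotherapy in the Flebogrif arm, whose counting does not depend on the wording.

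| Wording of the item | Flebogrif | EVLA | Difference |
|---|---|---|---|
| Polidocanol only (current) | p | s·p | p(1 − s) |
| Any agent used | p | s·p + l | p(1 − s) − l |

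The two differences differ by l. The distortion due to the wording is therefore the lidocaine reaction rate, and it does not depend on p or s.

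**Size.** The documents give neither p nor l, so the following is an assumed range. Suppose both rates equal r and no EVLA patient has sclerotherapy (s = 0). The current wording then shows a difference of r, and the agent-neutral wording shows zero.

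| Assumed r | Counted, Flebogrif (155 × r) | Counted, EVLA | Lidocaine reactions left out (155 × r) | Difference shown by current wording |
|---|---|---|---|---|
| 0.1% | 0.16 | 0 | 0.16 | 0.1 points |
| 0.5% | 0.78 | 0 | 0.78 | 0.5 points |
| 1% | 1.6 | 0 | 1.6 | 1.0 points |
| 2% | 3.1 | 0 | 3.1 | 2.0 points |

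If 30% of EVLA patients had polidocanol sclerotherapy (assumption), the difference shown falls to 0.7 × r, that is 0.07 to 1.4 points. The lidocaine reactions left out are unchanged.

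**Could it produce a falsely significant test?** With 155 per arm, Fisher's exact test gives a two-sided p of 0.060 for 5 versus 0 events and 0.030 for 6 versus 0, so six are needed. With no events counted under EVLA, the binomial chance of six or more among 155 Flebogrif patients is about 0.01% at r = 0.5%, 0.5% at r = 1% and 9% at r = 2%. It is negligible at r = 0.1%.

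**The case against.** The strongest reply is that one item's wording does not bias the complication comparison. A reader might infer from the item that the comparison as a whole is tilted against Flebogrif. The article does not support that. It lists ten separate items and states no any-complication composite through which one item could move an overall result. The list also carries skin burn and nerve injury, which the Introduction links to endothermal ablation. These do not repair the allergy item: they are worded without a cause and can count in either arm. But they do rule out a claim of net tilt.

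Three further points stand in part.

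- EVLA patients can have a countable polidocanol reaction after side-branch sclerotherapy, so the item is not closed to that arm. A lidocaine reaction still cannot count.
- Known polidocanol allergy is excluded, which should lower the polidocanol count. It does nothing for lidocaine.
- All adverse events are recorded, so a lidocaine reaction need not be lost. A reader might go further and conclude that it could never be compared between arms. That would argue from silence, since adverse event tables are commonly left to the full protocol or the analysis plan, and neither is shown. What stands is that the two drugs' reactions are gathered and classified differently.

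It might also be inferred that the item hides part of the benefit the trial sets out to show. The Introduction's objection to tumescent anaesthesia is that giving it can be painful, and pain has its own outcomes. Allergy to lidocaine is not part of the stated rationale.

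Finally, the equal rates in the illustration are an assumption. If lidocaine reactions are much rarer than polidocanol reactions, most of any observed difference is real and correctly counted.

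**Conclusion.** The point holds for the allergy item only. As worded, it can register a reaction to the drug in the Flebogrif procedure and cannot register one to the tumescent drug in the EVLA procedure, although complications are compared between arms. The distortion equals the lidocaine reaction rate, which the documents do not give. Over an assumed 0.1% to 2% it is 0.1 to 2 percentage points, or 0.2 to 3.1 uncounted events among 155 EVLA patients. It is probably small, and at assumed rates of 1% or less a falsely significant test is very unlikely.

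The primary outcome is anatomical, and the safety outcome covers DVT, pulmonary embolism and nerve injury. Neither they nor the sample size are affected. This is a minor point about a definition.

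**What to change.** In the Complications outcome, replace the polidocanol-specific item with *allergic reaction to any agent used in the procedure*. Make clear that agents used for later side-branch sclerotherapy are included, so that no reaction countable today is lost. Record the agent for each reaction and compare the item between arms with the tests already named. Recode allergic reactions already recorded as adverse events into this item before the analysis.

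The cost is one changed line in the outcome definition and one changed option in the electronic case report form, made while the trial is running. Enrolment began in September 2021 and was expected to finish around October 2024, so many patients will have been treated before any change. For them, lidocaine reactions rest on spontaneous or observed adverse event reports and may be under-counted relative to polidocanol reactions. The trial report should say so and give the date of the change. No procedure, other endpoint or sample size figure changes.
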